## Abstract

**Background:**

Quebec is one of the Canadian provinces with the highest rates of cancer incidence and prevalence. A study by the Rossy Cancer Network (RCN) of McGill university assessed six aspects of the patient experience among cancer patients and found that emotional support is the aspect most lacking. To improve this support, trained patient advisors (PAs) can be included as full-fledged members of the healthcare team, given that PA can rely on their knowledge with experiencing the disease and from using health and social care services to accompany cancer patients, they could help to round out the health and social care services offer in oncology. However, the feasibility of integrating PAs in clinical oncology teams has not been studied. In this multisite study, we will explore how to integrate PAs in clinical oncology teams and, under what conditions this can be successfully done. We aim to better understand effects of this PA intervention on patients, on the PAs themselves, the health and social care team, the administrators, and on the organization of services and to identify associated ethical and legal issues.

**Methods/design:**

We will conduct six mixed methods longitudinal case studies. Qualitative data will be used to study the integration of the PAs into clinical oncology teams and to identify the factors that are facilitators and inhibitors of the process, the associated ethical and legal issues, and the challenges that the PAs experience. Quantitative data will be used to assess effects on patients, PAs and team members, if any, of the PA intervention. The results will be used to support oncology programs in the integration of PAs into their healthcare teams and to design a future randomized pragmatic trial to evaluate the impact of PAs as full-fledged members of clinical oncology teams on cancer patients’ experience of emotional support throughout their care trajectory.

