This action-research intervention [29], inspired by realistic evaluation methodology [30–32] aims to evaluate the feasibility of integrating PAs within health and social care oncology teams and will be conducted in close collaboration with the actors on the ground. The specific objectives are to: 1) describe the mechanisms of co-constructing the implementation processes of the PA program; 2) identify factors that facilitate and hinder the integration and participation of PAs in health and social care oncology teams; 3) assess the effects of the PA intervention on the patients, the PAs, the healthcare team, the administrators, and the clinical organization of care; 4) identify ethical and legal issues of integrating PA in healthcare settings.

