## Methods/design

### Study design

The planned approach is a longitudinal multiple in-depth case study with two levels of analysis (clinical and organizational) that will be conducted over 4 years at six different sites. The longitudinal design is necessary to account for inevitable delays over the course of the implementation, to allow the time to consolidate changes made at each case site, and to allow the time needed to avoid making premature conclusions regarding the impacts of the changes [38, 39]. The multiple case study design allows for the in-depth analysis of the implementation processes in diverse oncology contexts. Qualitative and quantitative data will be used to document the intervention for each case, to examine the implementation processes, in their respective contexts, and to report their respective effects at the clinical and organizational levels [40]. This design is consistent with realistic evaluation [30] and intervention action-research [29] and structures our in-depth investigation of the links between the implementation and co-construction mechanisms and our ability to capture the challenges and the effects of the intervention.

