### Participants

For each setting, the representatives of high/mid-level managers working in the targeted program, the health and social care professional (HSP) team members, the patients, and the PAs (to be recruited) will be invited to participate in the project. For the patients, the inclusion criteria will be understanding written and spoken French, undergoing cancer screening or treatment, being at least 18 years old and have had at least one meeting with a patient advisor. All participants meeting the inclusion criteria will be invited to participate. This is therefore a consecutive sampling. Professionals and patient advisors will be approached by email. Patients will be approached by telephone or face-to-face through the patient advisor at their initial meeting. All participants will sign an informed consent form approved by Centre Hospitalier de l’Université de Montréal’s research ethics committee. Indeed, this study was submitted to and approved by the Centre Hospitalier de l’Université de Montréal’s research ethics committee.

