	Kessler Psychological Distress Scale (K6) [49]	• on emotional states	6 items	5 point Likert scale (1 = Always and 5 = never)	T0, T1, T2	Additional file 4: T0: 141 to 146 T1: same as T0 T2: same as T0
**PA reported experience**	PAs’ care experience questionnaire ^a^	• Site of diagnosed cancer; time of diagnostic; type of treatment; date of start of treatments • Consultation in oncogenetics, genetic status, time of disclosure of results of genetic testing, surgery to reduce the risk of developing cancer, time of preventive surgery • Evaluation of information communicated by medical team, support of friends and family.	25 items	Varied	T0	Additional file 5: T0: 39 to 60
	Sociodemographic questionnairev	• Gender, age, country of origin, region, number of people in the household, number of dependents, household situation, level of education, perception of financial situation.	18 items	Varied	T0	Additional file 5: T0: 19 to 36
	Previous personal experience with PAs questionnaire^a^	• Presence of pairing or not with a PA • Topics discussed, benefits and perceived contribution of PA • Expectations of patients that did not benefit from PA accompaniment are also evaluated	14 items	Varied	T0	Additional file 5: T0: 62 to 82
	Kessler Psychological Distress Scale (K6) [49]	• Psychological distress	6 items	5 point Likert scale (1 = Always and 5 = never)	T0, T2	Additional file 5: T0: 84 to 89 T2: idem to T0
	Review of PA experience with patient questionnaire^a^	• Support of clinical team • Quality of tools used • Useful information to effectively carry out their role as PA • Communication with the clinical team • Role in the clinical team • Perceived impact of their intervention on the patient and on the PA themself.	140 items	Varied	T2	Additional file 5: T2: 91 to 241
**Descriptive data of each meeting**	Logbook^a^	• PA name • Patient name • Date, time, duration • Context of the request • People present during the meeting • Context of the meeting • Step of patient trajectory • Topics discussed • Difficulties and questions • Feedback from the clinical team	28 items	Varied	After each meeting	Additional file 6: 3 to 42

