#### Questionnaires for patients

Measurements will be taken before the meeting with the PA (T0), immediately following this meeting (T1), and again 1 month after this meeting (T2). Two of the questionnaires used will be co-constructed with patients specifically for this study and assess: patients’ care experience (Additional file 4, questions 41 to 67) and patients’ experience with PAs (Additional file 4: questions 69 to 100 and 102 to 127), following the procedures and sequence of content validation outlined by Haynes and colleagues (1995) [53]. Three validated questionnaires will be used to assess patients’ psychological distress (K6) [49] (Additional file 4: questions 141 to 146), treatment adherence [47] (Additional file 4: questions 148 to 159), and ability to cope with cancer (CASE) [48] (Additional file 4: questions 129 to 140). Data variables of patients’ sociodemographic and clinical characteristics will be collected including sex, age, and type of cancer (Additional file 4, questions 22 to 39). To obtain a complete data set for 30 to 50 patients per site and based on a previously established response rate of 70% [54, 55], we will plan to recruit at least 40 to 70 patients from each site.

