### Quantitative analyses

Statistical analyses will be performed using IBM SPSS Statistics version 25 [58] and SAS 9.4 [59]. Results with *p* < 0.05 will be considered significant. Descriptive statistics will be used to summarize each setting’s patients’ and PAs’ socio-demographic and clinical variables and the health and social care providers’ professional experience. Student t tests or non-parametric tests, such as the Mann-Whitney test, will be used for continuous variables. At the organizational level, the challenges encountered throughout the implementation of the PA program and the engagement and satisfaction of the health and social care oncology teams will be examined. At the clinical level, the effects on the patients, the PAs and the health and social care oncology teams will be assessed.

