## Conclusion

Given oncology patients’ needs to be able to count on educational, emotional and partnership support over the course of their care trajectory, it is necessary to develop research projects that involve the various stakeholder groups and that yield results that decision makers can act on quickly. This study will evaluate the feasibility of integrating PAs into clinical oncology teams and highlight this integration procedure to identify the factors which enable or hinder their integration, to identify ethical and legal issues and means to address them, and to explore the effects of PA on patients, the PAs themselves, the care team, the administrators, and the organization of care. Should the results be promising, we will use them to plan and conduct a pragmatic randomized trial of the integration of PAs into clinical oncology care teams, to measure the impact of PAs integration on the teams on patients, and to better understand how this integration can improve the quality, safety and performance of our healthcare systems.

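### Patients are followed as one uncontrolled before-after group, so the planned significance tests can describe change but cannot show an effect of the patient advisor (PA)

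*Protocol article*

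**What the plan says.** The article describes a "longitudinal multiple in-depth case study with two levels of analysis (clinical and organizational) that will be conducted over 4 years at six different sites". Objective 3, at the end of the Background, is to "assess the effects of the PA intervention on the patients, the PAs, the healthcare team, the administrators, and the clinical organization of care". The abstract gives part of that task to the questionnaires: "Quantitative data will be used to assess effects on patients, PAs and team members, if any, of the PA intervention". The Quantitative analyses section sets p < 0.05 as significant, names Student t tests or non-parametric tests such as Mann-Whitney for continuous variables, and adds: "At the clinical level, the effects on the patients, the PAs and the health and social care oncology teams will be assessed".

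On who is measured and when, the Participants section includes among its patient criteria "being at least 18 years old and have had at least one meeting with a patient advisor". The section on patient questionnaires gives the schedule: "Measurements will be taken before the meeting with the PA (T0), immediately following this meeting (T1), and again 1 month after this meeting (T2". Table 1 places psychological distress (K6), coping (CASE) and treatment adherence at all three times. The target is 30 to 50 complete data sets per site at six sites.

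On use of the results, the Conclusion says: "Should the results be promising, we will use them to plan and conduct a pragmatic randomized trial".

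**The concern.** An effect is a contrast between what happened and what would have happened without the PA. For patients, the plan observes only the first. Those enrolled are in cancer screening or treatment. Within a month a result may arrive, a treatment phase may start or end, and usual care and personal adaptation continue. K6, coping and adherence can all respond to these events, in either direction. A fall in distress may be read as a PA benefit when there is none, or a hard treatment phase may hide a real one.

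This is not a detail that an analysis plan could settle, because no analysis plan can supply an unexposed group. What is at stake is what objective 3 may conclude. The results are also meant to support oncology programs in integrating PAs and to help design the later randomized trial, so a misattributed change could travel beyond this study.

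**Working it through.** **1. Is there a comparison group?** Set side by side, the Study design, Participants and Questionnaires for patients sections describe six cases, patients who have all met a PA, and measurements tied to that meeting. None describes an unexposed group, a pre-implementation series or a second baseline. Table 1 does mention expectations of patients who were not accompanied by a PA, but the inclusion criterion rules such patients out, so they are no control. The section on study challenges does not mention attribution.

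**2. The plan's own figures.** There is no effect size, SD or power to reproduce. The only patient-number calculation is recruitment at 70% response: 30/0.70 = 42.9, so 43, and 50/0.70 = 71.4, so 72, against a stated 40 to 70. That difference does not bear on this point. Pooled complete data would be 6 × 30 = 180 to 6 × 50 = 300 patients.

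**3. How small a change reaches p < 0.05?** For a paired t test, the smallest significant mean change, in SDs of the change scores, is t(0.975, n−1)/√n: 0.373 at n = 30, 0.284 at n = 50, 0.147 at n = 180 and 0.114 at n = 300.

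**4. How often would natural change alone be significant?** Assumptions, none of them in the documents:
- two-sided 5% paired t test of T0 against T2;
- natural fall d = 0.1 to 0.3 baseline SD, with equal SDs at both times;
- T0-T2 correlation r = 0.5 to 0.7;
- no PA effect;
- clustering by site and by PA ignored.

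Standardized change: dz = d/√(2(1−r)). Noncentrality: dz × √n. The probability of a significant fall is the upper tail of the noncentral t distribution beyond t(0.975, n−1).

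Example: d = 0.2, r = 0.5, n = 180 gives dz = 0.2/√1 = 0.2, noncentrality 0.2 × 13.42 = 2.68, critical value 1.97, probability 76%. Example: d = 0.1, r = 0.7, n = 30 gives dz = 0.1/0.775 = 0.129, noncentrality 0.129 × 5.48 = 0.71, critical value 2.045, probability 10%.

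| Complete patients | d = 0.1 | d = 0.2 | d = 0.3 |
|---|---|---|---|
| 30 (one site) | 8–10% | 18–28% | 36–54% |
| 50 (one site) | 10–14% | 28–43% | 55–77% |
| 180 (pooled) | 27–41% | 76–93% | 98–99.9% |
| 300 (pooled) | 41–61% | 93–99% | over 99% |

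Each range runs from r = 0.5 to r = 0.7. The nominal rate is 5% for both directions together, hence 2.5% for falls alone. By symmetry, a natural rise of the same size would be significant as often in the other direction and would offset a real benefit.

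**The case against.** The best defence is that the study does not claim much. The abstract says the effects are to be assessed if any exist, the conceptual framework speaks of potential effects, and the Conclusion of exploring them. The overall aim is feasibility, and impact is left to a later randomized trial. Objective 3 also draws on interviews, focus groups and the research logbook, with triangulation, in a realistic-evaluation frame. T1, immediately after the meeting, leaves no month for natural change between T0 and T1. The article does not say that T0-T2 change equals the PA effect, nor which contrast the tests serve; Mann-Whitney compares independent groups. It does not state a pooled test either, and the targets are per site.

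Most of this stands and limits the point. It does not remove it. Allowing that there may be no effect is different from being able to tell an effect from background change. T1 shortens the interval, but measurement error and expectancy remain, and T1 says nothing about a benefit at one month. Triangulation gives context and mechanism but no quantitative counterfactual.

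A reader might infer three stronger things that the documents do not support:
- **That patients enter at a peak of distress, so K6 is bound to fall.** The article describes consecutive sampling with no distress threshold or need-based referral, and gives no K6 course.
- **That p < 0.05 triggers the randomized trial.** The sentence on promising results follows a list of feasibility, barriers, ethical and legal issues, and explored effects; it is not tied to significance.
- **That the observed change will be the later trial's effect size.** The abstract says only that the results will be used to design that trial.

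**Conclusion.** The point holds as one about attribution. Eligibility, schedule and the absence of any comparison group are all stated or plain from the text, and together they cannot deliver the patient part of objective 3 as worded. The bias could run either way.

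Its size cannot be fixed from the article. The table shows sensitivity, not a forecast: modest background change would often pass as significant in a pooled analysis and less often at a single site. The figures depend on the assumed correlation and shift, on a paired test the article does not name, and on ignoring clustering. The feasibility aim, hedged wording, T1 and qualitative sources make this a matter of correcting the stated inference; they do not call the design itself into question.

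**What to change.** - **Abstract, objective 3 and Quantitative analyses:** state that patient results at T0, T1 and T2 describe within-group change, are reported with confidence intervals, and are not attributable to the PA.
- **Conclusion:** state that the judgement that results are promising rests on feasibility, acceptability and the qualitative findings, and that the uncontrolled change will not by itself serve as the effect size for the randomized trial.
- **Optional:** describe change by treatment phase or by PA meetings, using items already collected such as treatment start date and the logbook entry "Step of patient trajectory". Label this exploratory. It does not restore attribution, since the number of meetings may itself reflect need.

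The cost is a few sentences, with no new recruitment or data collection. The downside is a more modest claim for objective 3.

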**Discussion:**

This study will be the first to integrate PAs as full-fledged members of the clinical oncology team and to assess possible clinical and organizational level effects. Given the unique role of PAs, this study will complement the body of research on peer support and patient navigation. An additional innovative aspect of this study will be consideration of the ethical and legal issues at stake and how to address them in the health care organizations.

**Supplementary Information:**

The online version contains supplementary material available at 10.1186/s12913-020-06009-4.

## Background

Quebec is one of the provinces in Canada with the highest rates of cancer incidence and prevalence. In 2019, 55,600 Quebecers received a cancer diagnosis [1]. Given that prevention and treatment of cancer are public health priorities in Quebec, the provincial ministry of health and social services has developed a strategic plan for the fight against cancer, namely the Quebec cancerology Program (PQC). The PQC includes a framework and an action plan to reduce the incidence and prevalence of cancer, as well as to improve the quality (accessibility, effectiveness, efficiency, relevance, person-centered care), safety (treatment errors, health care acquired infections), and experience of care and services for cancer patients [2, 3]. One way to help improve the experience of care and services is through Patient-provider partnerships which go beyond patient-centered care and include: 1) recognition of patients’ experiential knowledge; 2) survivors’ status as full-fledged members of the care and services team; 3) patients’ role as one’s own care giver; and 4) patients’ capacity for self-determination for making decisions concerning themselves according to their needs and values [4]. One application of the patient-provider partnership approaches to engage patients who have experienced a health problem and the health care system to help those with similar problems get through their experience or to participate in committees to improve the quality and safety of care. Patients are already well integrated in oncology governance committees in Quebec [5], but the integration of patient advisors in care and services teams has not been fully achieved.

Some studies show the potential of including patient advisors in clinical oncology teams to facilitate communication between patients and their health and social care team, and to improve the experience of care for patients with cancer as well as those at high risk for developing this disease, particularly in terms of information sharing, emotional support [6–12], and engagement in their care [13]. PA interventions are even more relevant since emotional support is an unmet need of people who have to deal with cancer [14].

Kowitt and collaborators’ 2019 study reveals that peer support is very common in all phases of the oncology continuum of care [9]. This support is usually provided by “Patient Navigator” programs where the patient navigator’s main role is to help patients access care; thereby, reducing the time to receive a diagnosis and treatment and reducing the number of patients lost to follow up [15–18]. Moreover, these navigators can include nurses, social workers, educators, as well as former patients [19]. These programs [19] have been shown to improve provide comfort to patients [6], increase adherence to treatment [20], improve their health [21, 22], help them find their way in the healthcare system [7], reduce wait times [20], and lower hospital readmission rates [23]. Such programs tend to focus on underprivileged groups, rather than targeting all cancer patients [24].

In oncology, patient advisors (PA) programs are similar to patient navigator ones, but in addition they consider PAs as being integral members of the clinical team with the skills to help other patients navigate their health situation [25]. Thus, PAs play a distinct and innovative role comparable to that of peer helpers in mental health contexts [23, 26]. A study carried out at the Centre of Expertise for Traumatic Amputation Victims Requiring Emergency Microsurgical Re-implantation (CEVARMU) in Quebec showed that including PAs on the health and social care team had positive impacts on the patients, the PAs, the health care professionals, the administrators, and the decision-makers [27]. Among the main advantages observed were the reduction of depressive symptoms, the reduction of pain and anxiety, the improvement of quality of life, treatment compliance, and healthy lifestyle habits [28]. However, this study also highlighted ethical and legal issues related to the status of PA and the limits of their role. The feasibility, acceptability, impacts and ethical/legal issues of the integration of patient advisors in oncology remain to be explored and documented.

This action-research intervention [29], inspired by realistic evaluation methodology [30–32] aims to evaluate the feasibility of integrating PAs within health and social care oncology teams and will be conducted in close collaboration with the actors on the ground. The specific objectives are to: 1) describe the mechanisms of co-constructing the implementation processes of the PA program; 2) identify factors that facilitate and hinder the integration and participation of PAs in health and social care oncology teams; 3) assess the effects of the PA intervention on the patients, the PAs, the healthcare team, the administrators, and the clinical organization of care; 4) identify ethical and legal issues of integrating PA in healthcare settings.

